## Abstract

**Background:**

In recent years, there has been a significant change in the demographics of developed countries, including an increase in the number of older people. This aging population and the associated need for medical care and assistance places great strain on health care systems worldwide. In older populations, improved knowledge and understanding of the relationship between moderate exercise and health might result in greater motivation to engage in such activity; thus improving the overall health of this population. The aim of the proposed project is to assess the degree of improvement in functional performance through physical training with verbal stimulation, as well as the possibility of changing habitual ways of spending free time, in older people under institutional care.

**Methods:**

Study participants aged 65–85 years, who are living a sedentary lifestyle in care homes in Southeast Poland, will be invited to participate in this randomized controlled trial. Those who meet the eligibility criteria and are enrolled in the study will be assigned at random to one of four parallel groups: (1) basic exercises combined with verbal stimulation, (2) basic exercises without verbal stimulation, (3) functional exercise training with verbal stimulation, and (4) functional exercise training without verbal stimulation. Participants will engage in 30-min workouts, twice per week, for 12 weeks. Tests will be done: (1) before exercises, (2) after 12 weeks of exercises, (3) 12 weeks after the end of the exercises, and (4) 24 weeks after the exercises. Primary outcome measures will include the Short Physical Performance Battery (SPPB). Secondary outcomes will include the Physical Activity Scale for the Elderly (PASE), the Timed Up and Go (TUG) test, the 10-Meter Walk test (10MWT), the Back Scratch (BS) test, the Chair Sit and Reach (CSR) test, the Grip Strength (GS), and the Berg Balance Scale (BBS). Other outcomes will include results regarding postural stability from the stabilometric platform and quality of life (SF-36).

**Discussion:**

Our study will help to determine the effectiveness of the training programs, particularly in relation to participants’ motivation to exercise.

**Trial registration:**

The Sri Lanka Clinical Trials Registry, ID: SLCTR/2016/004. Registered on 12 February 2016.

**Electronic supplementary material:**

The online version of this article (doi:10.1186/s13063-017-2114-1) contains supplementary material, which is available to authorized users.

## Background

Population aging is one of the greatest social and economic challenges facing the European Union (EU). Projections foresee a growing number of persons aged 65 years and over, with a particularly rapid increase in the proportion aged 85 years and over. These demographic developments are likely to have a considerable impact on the health care requirements of older people [1]. According to a 2011 report by the Central Statistical Office in Poland, nearly 40% of people older than 70 years of age have problems with basic self-care: more than 1.8 million have difficulty self-washing, and more than 1.6 million have difficulty dressing and undressing independently [2].

Reduced or impaired mobility leads to poorer quality of life among older people living in residential care homes. Almost 90% of people in long-term care have some type of reduced mobility [3], with about 40% of those with dementia losing their ability to walk each year [4]. Immobility contributes to a loss of ability to perform basic and instrumental activities of daily living and an increased risk of falls and health problems [5]. The adverse consequences of immobility and bed rest are well established; however, older residents living in care homes still spend most of their time in wheelchairs or in bed [6].

Physical activity is an effective strategy for delaying and preventing functional limitations associated with aging. If performed regularly, general physical activity becomes easier. According to the European Opinion Research Group, 97.4% of people aged 65 and over do not meet recommendations for physical activity to achieve health benefits [7]. A Polish study, by Kozdroń, demonstrated that only 7% of people aged 60–64 years and only 0.6% of those aged 80 years or older undertake regular physical activity [8]. In the older Polish population, the most popular use of free time is watching television and listening to the radio (30.2%), followed by reading (15.5%), passive recreation (13.1%), religious practices (11.9%), and gardening (8.7%) [9].

Although physical activity is a part of healthy aging, physical activity levels often significantly decrease with age [10]. According to Ingrid et al. [11], in older people, a lack of participation in regular physical activity is associated with a decline in physical functioning and problems with the ability to perform day-to-day activities. Weeks et al. [12] found that the physical activity levels of older residents living in care homes were lower than those living in the community. Chen points out that institutionalized residents often lead a repetitive lifestyle that lacks variety, which imposes restrictions on activity choices [13]. In another study, the wellbeing and subjective assessments of the quality of life of the study participants was demonstrated to depend on the degree of physical activity of the respondents [14].

In the older population, the low level of knowledge and understanding of the relationship between physical activity and its impact on health may be a barrier in itself. According to Allender, older people have no knowledge about the “proper” amount of physical activity for them, and believe that the activities that they perceive as an “activity” are aimed at younger people [15]. Resnick et al. found that seniors spent increased time partaking in physical activity after the implementation of an incentive program and exercises [16]. According to Dishman, the awareness of the benefits of movement translates into long-term involvement in exercise [17]. Knowledge and belief in the health benefits of physical activity appear to be helpful in motivating an older person to take up exercise on a regular basis.

The most effective classical interventions to improve physical functioning consist of physical exercise, through improved balance, strength and walking practice [18]. According to Westcott systematic strength training positively affects the self-esteem and cognitive abilities of older people [19]. As a result, undertaking physical activity reduces the risk of the development of sarcopenia and related adverse changes. Resistance and similar exercises result in improved gait speed [20]. In their systematic review of 901 care home residents, Brett et al. reported physical exercise to have significant positive effects on cognition, agitation, mood, mobility, and functional ability [21]. de Vreede et al. [22] and Zak et al. [23] conclude that functional task training is the best form of physical exercise; however, de Oliveira et al. [24] report 12 weeks of physical training to have a beneficial effect on the functional state of older people.

Despite being the most effective means of promoting participation in physical activity, at present there are no systematic education and exercise programs designed to improve and maintain functional capacity in Polish care homes for older people. The use of simple, inexpensive and widely practicable exercises and models of motivation for older people in care homes could significantly improve their chances of maintaining or prolonging their independence in performing basic everyday activities and maintaining a good quality of life.

### Objectives

The aim of the project is to assess the degree of improvement in functional performance and the possibility of changing habitual ways of spending free time among older people under institutional care, by applying physical training with verbal stimulation.

## Methods

The study protocol has been written in accordance with Standard Protocol Items: Recommendations for Interventional Trials (SPIRIT). A SPIRIT Checklist is provided in Additional file 1.

### Trial design

The research will take the form of a randomized controlled trial with four open-label, parallel groups. Data will be collected at baseline and at 12, 24, and 36 weeks following completion of the program. The Consolidated Standards of Reporting Trials (CONSORT) Statement has been used as a framework for the development of the methodology for this study [25]. The study protocol is illustrated in Fig. 1

**Fig. 1 Fig1:**
[figure not shown]
Flow diagram of the study protocol

### Recruitment

Selected care homes for older people and the chronically physically ill in Southeast Poland will be included in the study. The group of ten nursing homes will be randomly selected. In the case of an insufficient number of participants, another draw will be conducted and the previously chosen residential home will be excluded. Management centers will be informed about the purpose and conduct of the study. After obtaining approval for the project, each center will begin recruiting participants and promotional activities. Pre-qualification for participation in the study will be carried out by a physiotherapist working in the center. A physician employed in a nursing home, after consultation with the research team, will be required to give express written consent to the participation of selected older people in the project, taking into account lack of contraindications to physical exercise. After obtaining written permission from the physician for inclusion in the program, the consent of the study participants prior to baseline assessment will be obtained.

### Participants

Participants eligible for the trial must comply with the following criteria at randomization:Residents of care homes for older people and people with chronic illnessesAged 65–85 yearsMini-Mental State Examination (MMSE) score > 19Geriatric Depression Scale (GDS) score < 20 pktSpend free time sitting at least 4 h/day, 6 to 7 days/week (Physical Activity Scale for the Elderly (PASE))

Exclusion criteria:Severe systemic diseaseSevere circulatory or organic insufficiencySevere neurological disorderLack of consent by the older person or their physician

### Interventions

The subjects will be assigned, at random, to one of four groups:Arm 1: basic exercises combined with verbal stimulationArm 2: basic exercises without verbal stimulationArm 3: functional exercise training with verbal stimulationArm 4: functional exercise training without verbal stimulation

Figure 2 shows the overall schedule and time commitment for trial participants.

**Fig. 2 Fig2:**
[figure not shown]
Overall schedule and time commitment for trial participants

### Exercise program

#### Basic exercises

The program will include exercises performed in a sitting position. Exercises will contain elements of aerobic, stretching, and equivalent exercises.

#### Functional exercise program

Training will be divided into two sessions. Session I will involve strengthening and stretching, with exercises performed in a sitting position using a Thera-Band and gymnastic sticks. Session II will involve equivalent and functional training using exercises performed in a seated or standing position, using chairs as stabilizing aids. The exercises will contain complex movements that older people perform as a regular part of everyday activity. A single “Session I” and a single “Session II” will take place each week.

The exercise program will be conducted in groups of four to eight, in the care setting, by a qualified physiotherapist. Frequency of training: twice a week for 30 min. Intensity of effort on the Borg Scale: 11–13 points. The frequency of training was determined based on a review by Liu et al. [26]; the intensity of exercise (moderate) was selected in accordance with Canada’s Physical Activity Guidelines [27]. Before and after each workout, blood pressure will be taken and heart rate will be recorded.

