The verbal stimulation model to be implemented in the presented study is based on the research of Park et al. [30], and will include the following:An assessment of the study participant’s perception of their own performance of the functional activity; specifically, whether the participant perceives their starting position, movement, and final position to have followed the correct motion pattern. The participant will be asked: “Do you feel that you performed your task well?” The question is intended to increase internal motivationA qualitative assessment of task performance will consist of the study participant determining the goal of the activity, and answering the question: “Is the quality of the task you fulfilled, good?” This question is intended to increase internal motivation by connecting their achievement with satisfactionAn assessment of the perception of one’s (the study participant’s) own functional activity in accordance with their capability of performing specific tasks. The process will consist of determining the degree of difficulty of the task and evaluating whether performance of the task, despite the degree of difficulty, is feasible. If a task is found to be infeasible, it will be divided into simpler parts. Gradation of difficulty will allow the execution of the task and should allow the participant to generate a more positive association with the activity, helping to eliminate anxiety related to undertaking exercise [32]Provision of support for group members. Each group will be encouraged to focus on one purpose: to increase the functional activity of themselves and each other

According to Locke, raising an older person’s need for physical activity may be achieved by increasing awareness of the motion aspects of human movement and discussing anxieties associated with undertaking physical activity [33].

During the exercise program, physiotherapists will discuss any unpleasant sensations associated with the exercise. Older people will be provided with information explaining how they can reduce pain associated with the activity, if experienced (e.g., hot/cold compresses). Seniors will also be guided as to how to develop a realistic attitude toward the adverse effects of intensified exercises (e.g., muscle pain will not cause further damage to bones or joints).

Verbal stimulation is meant to provide positive stimulation to achieve the success associated with the activity and to overcome any fear of the activity [34].

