The verbal stimulation program will be included in the individual exercise programs. The physical exercise programs will be carried out by physiotherapists (one therapist at the nursing home) with at least 2 years of experience in exercise training of older people. Each of the therapists will be trained in exercise programs and verbal stimulation before the start of the program. The intervention will be considered complete if the participant attends at least 80% of the sessions [35, 36]. Therapists will take charge of logging and assessing the attendance of older people at the exercise programs.

The interventions described above involve low risk in relation to health and life. For the duration of the examination, each of the leading therapists will monitor the somatic symptoms of the participants, and determine which directly result from the intervention. Each incident will be dealt with individually and recorded in the protocol of adverse events. In the event of health problems, such as pain or malaise caused by excessive effort, the physician supervising the study will decide on participant exclusion.

During the trial, patients will be advised not to take part in the other group physical activities. Monitoring activities will be conducted therapists responsible for group exercises in the nursing home.

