### Sample size

An a-priori power analysis was conducted to determine the sample size necessary to find statistically significant exercise effects [52]. The sample size calculation is based on the primary outcome and analysis. The sample size was chosen according to the Cohen method, using standard assumptions: 0.05 for significance level, 0.8 for power of test, 0.5 for effect size which accounts, according to Cohen, for medium effect size. For the final analysis, the total participant number will be 156 (39 in each arm). To allow for a 25% dropout rate, 208 senior participants will be recruited.

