### Randomization

Randomization will be carried out by stratified sampling using the statistical package R, version 3.2.2. To obtain an equal distribution of senior subjects across the study groups, the allocation will be performed as block randomization. We will use four-in-one blocks. To solve the problem of predicting the next assignment, the allocator will hide the block size from the executer and use randomly mixed block sizes. Randomization order will be determined using a computer-generated random number schedule. Randomization will be performed by a biostatistician not participating in the study. This person will not participate in the conduct of the research, nor will they be involved in the implementation of the exercise programs. The same person will be responsible for ensuring that the participant list remains confidential. Staff performing outcome measurement and data analysis for the primary outcomes will be blinded to group allocation. However, due to the group nature of the care homes, it will not be possible to blind the participants.

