### Statistical methods

The basic characteristics of the groups will be established, and the means and medians will be calculated. The confidence intervals for the mean of quantitative variables will also be determined. Percentage distribution and the number of cases will be established for qualitative variables. To check the differences between the groups, an analysis of variance (ANOVA) will be used for normally distributed variables and a Kruskal-Wallis test for non-normally distributed variables. Normality will be assessed with a Shapiro-Wilk test. We will use the Bonferroni correction to appropriately adjust the overall level of significance for multiple comparisons. Alpha levels will be 0.05 and 0.01.

Basic interactions between the studied groups will also be explored. If there is no interaction, we will examine the independent effects of intervention. If there is significant interaction, the values of the coefficients in the multiple regression model will be tested. Interpretation of research results will be based on estimation and associated 95% confidence intervals.

The analysis will be performed on the ITT set. The analysis will be repeated per-protocol (PP) (in which participants who violate the protocol are excluded from the analysis set) and compared to the ITT analysis as a sensitivity analysis. The multiple imputation (MI) technique will used for dealing with missing data under the assumption that data are missing at random [53].

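### Residents train in small classes, but the stated between-arm test treats them as independent, so its error rate depends on class and home correlations that the article does not give

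*Protocol article*

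**What the plan says.** All of this is in the Protocol article.

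- **Delivery** (Functional exercise program): "The exercise program will be conducted in groups of four to eight, in the care setting, by a qualified physiotherapist". Sessions run twice a week for 12 weeks. Under Verbal stimulation, staffing is given as "one therapist at the nursing home". Recruitment gives ten homes.
- **Group mechanism** (Verbal stimulation, last of four listed components): "Each group will be encouraged to focus on one purpose: to increase the functional activity of themselves and each other".
- **Allocation** (Randomization): "Randomization will be carried out by stratified sampling using the statistical package R", in blocks, with residents as the unit. The strata are not named.
- **Analysis** (Statistical methods): "To check the differences between the groups, an analysis of variance (ANOVA) will be used for normally distributed variables and a Kruskal-Wallis test" for non-normal variables. A multiple regression follows if there is interaction, but its terms are not listed. Interpretation is to rest on 95% confidence intervals. No term for class, home, therapist or stratum appears.
- **Sample size**: "0.05 for significance level, 0.8 for power of test, 0.5 for effect size", giving "the total participant number will be 156 (39 in each arm"). No ICC or design effect is mentioned.

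**The concern.** Residents who exercise together twice a week for 12 weeks share a timetable, a pace, companions and, in two arms, deliberate peer support. Their SPPB scores may therefore be more alike than those of residents in different classes. Because the exercise programmes and the use of verbal stimulation differ by arm, a class will normally belong to one arm. Class-to-class variation then enters the arm means directly, and a one-way ANOVA or Kruskal-Wallis test does not allow for it.

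Homes act the other way. If each home contributes to all arms, home differences cancel from the arm comparison but still inflate the within-arm variance used as the yardstick.

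At stake are the p-value for the primary outcome and the width of every confidence interval on which interpretation will rest. If class membership is not recorded during the trial, it may not be possible to repair this afterwards.

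**Working it through.** **Inputs from the article.** 10 homes; 4 arms; classes of 4 to 8; 156 analysed (39 per arm); 208 recruited; d = 0.5; alpha 0.05, taken as two-sided.

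**Assumptions, not in the article.** Every home runs all four arms, with one single-arm class per arm per home. Class ICC (ρc) and home ICC (ρh) are varied.

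**The plan's own figures.** Recruitment: 156 / (1 − 0.25) = 208, which agrees. For 156 itself, a two-group comparison with d = 0.5, alpha 0.05 and 80% power needs 64 per factor level, so 128 in total for a main effect. The figure of 156 (78 per level) appears if alpha is halved to 0.025 for two main effects, which is an inference. Both calculations take residents as independent.

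**Class size.** Recruited: 208 / (10 × 4) = 5.2. Analysed: 156 / (10 × 4) = 3.9.

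**Direction of the error.** Set the total variance to 1, with H homes and m completers per class. The true variance of a difference between two arm means is 2[1 − ρh + (m − 1)ρc] / (Hm). The naive analysis uses approximately 2 / (Hm). The ratio of true to naive variance is therefore about

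1 + (m − 1)ρc − ρh.

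Above 1, the naive test rejects too often; below 1, too rarely. With m = 4 the two errors offset when ρh = 3ρc.

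**Simulated type I error** of the four-arm ANOVA, nominal 5%, 10 homes × 4 classes × 4 completers (160 residents):

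| Class ICC | Home ICC | Variance ratio | Naive ANOVA |
|---|---|---|---|
| 0.02 | 0 | 1.06 | about 6% |
| 0.05 | 0 | 1.15 | about 8% |
| 0.10 | 0 | 1.30 | about 11% |
| 0.05 | 0.05 | 1 + 0.15 − 0.05 = 1.10 | about 7% |
| 0.05 | 0.20 | 1 + 0.15 − 0.20 = 0.95 | about 4.6% |
| 0 | 0.20 | 0.80 | about 2.4% |

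Kruskal-Wallis, simulated for class ICC up to 0.10 and home ICC up to 0.10, behaved much like the ANOVA. Testing arms on class means with home as a block, which leaves (10 − 1)(4 − 1) = 27 error degrees of freedom, held about 5%. Adding home as a fixed effect without a class term did not: with both ICCs at 0.05 the error was 7.9%.

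**Power for a main effect**, d = 0.5, alpha 0.05, 78 per factor level, class effect only, dividing n by the design effect 1 + (3.9 − 1)ρc:

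- ρc = 0: n = 78, power 87%.
- ρc = 0.05: design effect 1.145, n = 78 / 1.145 = 68.1, power about 83%.
- ρc = 0.10: design effect 1.29, n = 78 / 1.29 = 60.5, power about 78%.

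If the inferred alpha of 0.025 is what was intended, the start is about 81%. With 4 per class it falls to about 75% (ρc = 0.05) and 69% (ρc = 0.10), by the normal approximation.

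**The case against.** - **The ICC is unknown, and so is the net direction.** This stands. A reader might infer that the planned p-values are certainly too small. The article does not support that. At class ICC 0.01 with 4 per class the standard error is off by only 1.5%, and class ICC 0.05 with home ICC 0.20 gives about 4.6%, close to nominal.
- **The layout is assumed.** This also stands. The article does not say that every home runs all four arms, that each class holds one arm, or that home is a stratum. One arm per class is implied only by the differing programmes.
- **One therapist per home looks like a second source of false positives.** On the layout assumed here it is not. A therapist who serves all arms in a home is crossed with arm, and the effect largely cancels from arm contrasts. The class is what inflates the error rate.
- **The power loss can be made to look larger.** Combining 156 analysed residents with the recruited class size of 5.2 gives about 80% and 74%. That mixes two populations; with 3.9 completers per class the figures are 83% and 78%. At class ICC 0.05 and alpha 0.05, power therefore stays above the planned 80%.
- **Peer support is a small part of the intervention.** Three of the four verbal-stimulation components concern the individual. That tempers the expected ICC but does not remove the shared sessions.
- **This is detail for a SAP.** That is true of covariates and degrees-of-freedom methods. It does not answer the main point: the article names the test, and Kruskal-Wallis cannot carry a class or home term. A SAP that followed the text would inherit the problem.

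**Conclusion.** The concern holds in conditional form. The article names an independence-based test for residents whom its own delivery model puts into classes. If outcomes correlate within class, the stated test rejects too often; if home differences are balanced across arms and omitted, it rejects too rarely.

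Over the assumed range, the true error rate of a nominal 5% test lies between about 2.4% and 11%, and the reader of the results would not know where. The loss of main-effect power is moderate at class ICC 0.05 and takes power just below 80% at 0.10. These figures rest on the assumed ICCs, the 10 × 4 single-arm layout and about 4 completers per class. The mismatch between delivery and test does not depend on the ICC values; its size does.

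**What to change.** 1. Add a class identifier to the attendance log that the therapists already keep, and state which homes run which arms and what the randomisation strata are.
2. Replace ANOVA/Kruskal-Wallis for SPPB with a linear mixed model containing exercise type, verbal stimulation and their interaction, baseline SPPB, home and any other randomisation stratum as fixed effects, and a random intercept for exercise class. Use small-sample degrees of freedom (for example Kenward-Roger), since the number of classes is limited.
3. Carry home and class into the imputation model, so that imputed values respect the same structure.

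Home as a fixed effect alone is not enough; the class term is needed.

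The cost is one field on an existing form and a change of analysis wording before the data are analysed. Recruitment was still open when the article was submitted. The downside is somewhat wider intervals if the class ICC exceeds zero; where homes differ, adjusting for home recovers some precision.
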